### Cost-utility analysis/Cost-effectiveness analysis

The cost-effectiveness analysis will consist of two components. 1) A bootstrap technique will be used to estimate the costs from a patient and health insurer's perspective. 2) A detailed cost-utility analysis, using a decision analytic model will be performed to estimate costs associated with primary and secondary outcomes. Ad 1) Differences in mean costs between both groups will presented with 95% confidence intervals estimated using bootstrapping methods [37]. Cost-effectiveness and cost-utility ratio's will be assessed from a patient's and health insurer's perspective. All direct and indirect costs will be taken into account. Differences in direct, indirect and total costs between groups will be computed with 95% confidence intervals by using bootstrapping methods. Cost-effectiveness planes and acceptability curves will be presented [38]. Ad 2) For the cost-utility analysis, a linear decision tree will be modelled using the TreeAge Pro Healthcare Module. Pathophysiological, quality of life and cost data from this study will be supplemented by data from the literature. The model will be build based on the same methodology as described in the papers by Herbst [39] and Culligan [40], in which decision analyses on macrosomia are discussed.

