**Discussion:**

If the FitFor2 intervention program proves to be effective, obstetricians and midwives should refer women at risk for GDM to a special exercise program. Exercise programs for pregnant women under supervision of an experienced trainer are already available in the Netherlands, and these programs could be adjusted easily for this target group. Furthermore, the costs of these programs should be refunded by including them in the basic health care cost reimbursement schemes.

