#### Questionnaire

• Physical activity will be assessed with the Activity Questionnaire for Adolescents & Adults (AQUA) [31].

• Quality of life will be assessed with the EuroQol [32,33].

• All costs related to pregnancy and delivery: direct health care and non-health care costs and indirect non-health care costs. Examples of direct health care costs are costs for visits to the general practitioner, medical specialists, therapists, dieticians, costs of medication and hospitalisation. Examples of direct non-health care costs are the costs of over-the-counter medication, travel time, and waiting time. Indirect costs will include the costs of absence from paid and unpaid work. Costs will be calculated by multiplying the volume of resource use by cost prices, following the Dutch guidelines for economic evaluations in health care to estimate costs [34].

• Potential confounding variables such as age, ethnicity, socio-economic status, working status, and parity will be measured also.

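### The cost ratios are declared from a patient's and a health insurer's perspective, but the stated cost set is all direct and indirect costs, which does not fit the insurer label

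*Protocol article*

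**What the plan says.** The section *Cost-utility analysis/Cost-effectiveness analysis* names the viewpoint twice. For the costs: "A bootstrap technique will be used to estimate the costs from a patient and health insurer's perspective". For the ratios, with the next sentence fixing what is counted: "Cost-effectiveness and cost-utility ratio's will be assessed from a patient's and health insurer's perspective. All direct and indirect costs will be taken into account". The section then promises component results: "Differences in direct, indirect and total costs between groups will be computed with 95% confidence intervals by using bootstrapping methods". It also announces cost-effectiveness planes and acceptability curves.

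The cost categories are defined under *Data collection*, *Questionnaire*. Direct health care costs cover such items as consultations, medication and hospital stays. A second group is non-medical: "Examples of direct non-health care costs are the costs of over-the-counter medication, travel time, and waiting time". The third is lost work: "Indirect costs will include the costs of absence from paid and unpaid work". No section assigns any of these categories to one perspective or the other, and none names a societal perspective.

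**The concern.** The perspective of an economic evaluation determines which costs belong in the numerator. An insurer's ratio should contain what the insurer pays or saves, and a patient's ratio what the patient pays or loses. A rule that counts every direct and indirect cost describes a societal total, which is neither of the two perspectives named.

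If the rule were applied as written, the insurer ratio could move for or against the programme because of travel time or work absence, which the insurer neither pays nor saves. The plane and the acceptability curve would inherit the same mislabelled costs. And because several numerators fit the wording, the choice among them would remain open after the data are seen.

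**Working it through.** The article gives no unit prices, cost totals or ratios, so there is no figure to reproduce. The check sets the cost categories against the two named perspectives. The last two columns follow from the nature of each cost; the article does not state them.

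| Cost category | Source in the article | Counted under the all-costs rule | Borne by a health insurer | Borne by the patient |
|---|---|---|---|---|
| Direct health care | *Questionnaire* | yes | as far as insured | any part she pays herself |
| Exercise sessions | *Intervention*; not itemised among the cost examples | assumed yes | yes, if refunded | otherwise, if charged to her |
| Over-the-counter medication | *Questionnaire* | yes | no | yes |
| Travel and waiting time | *Questionnaire* | yes | no | yes |
| Absence from paid work | *Questionnaire* | yes | no | only as far as she loses income |
| Absence from unpaid work | *Questionnaire* | yes | no | yes, as lost time |

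**Step 1: the numerators.** Write the between-group difference in each cost as H (insured direct health care), U (health care paid by the patient), E (delivery of the exercise sessions), O (over-the-counter medication), T (travel and waiting time) and W (work absence).

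- All-costs numerator: H + U + E + O + T + W
- Insurer numerator, with the sessions refunded: H + E
- Difference: U + O + T + W

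Divided by the between-group difference in effect, U + O + T + W is the amount by which a literal all-costs ratio departs from an insurer's ratio. None of its terms can be valued from the article. The sign is open too, since work absence could differ in either direction.

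**Step 2: does separate reporting repair this?** Only in part. The reported direct difference would be H + U + E + O + T and the indirect difference W. Subtracting W from the total still leaves O and T in the direct figure, because the *Questionnaire* section classes them as direct costs. The insurer's figure appears only if direct health care and direct non-health care costs are separated and U is taken out. *Outcome measurements* does list direct health care, direct non-health care and indirect costs as distinct items, so most of this split can be made from planned data.

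**Step 3: could the excluded terms differ between groups?** Yes, by design. Only the intervention group is offered two supervised sessions a week in hospital physiotherapy departments for the rest of pregnancy. With entry between 14 and 20 weeks and delivery assumed at 40 weeks, this is (40 − 20) × 2 = 40 to (40 − 14) × 2 = 52 visits at full attendance. If the questionnaire captures travel to these sessions, T will not cancel between the groups. This shows how a difference could arise; it does not estimate its size.

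**The case against.** The strongest reply is that the wording can be read without contradiction. The two perspectives together may be meant to cover all costs, with insured care on the insurer side and time, out-of-pocket and work-absence costs on the patient side. Or the first mention, which is in the singular, may describe one combined patient-and-insurer view. A one-paragraph economic plan in a journal article may also condense a fuller costing document. These points stand to this extent: a reader might infer that the insurer ratio will certainly contain work absence, and the article does not say so. They do not remove the conflict. Nothing in the text makes the patient-side allocation, and a combined view would still count paid-work absence without saying that either party bears it. Condensing can explain a missing item list, but not an explicit all-costs rule placed directly after an insurer perspective.

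A reader might also infer that the reimbursement recommendation rests on the insurer ratio. The abstract's discussion says that "the costs of these programs should be refunded by including them in the basic health care cost reimbursement schemes", but both it and the main *Discussion* make this conditional on the programme proving effective. Neither mentions an insurer ratio, so that stronger claim fails.

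Nor can a euro amount for the distortion be defended, since any figure would come entirely from assumed days and prices.

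Finally, the separate direct and indirect differences do soften the problem, because a reader could see whether work absence drives the total. They do not settle what enters each ratio.

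**Conclusion.** The point holds as a mismatch between two stated rules: the perspectives named are the patient's and the insurer's, and the cost set is societal if read literally. The conclusion rests on the *Questionnaire* definitions and on one assumption, that a health insurer does not pay for lost work, travel or waiting time, or over-the-counter medication. How far direct health care is insured is not described in the article, so the boundary between H and U has to be stated by the investigators.

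The size of any distortion is unknown and cannot be derived from the document. The consequence is confined to the cost-effectiveness and cost-utility results, a secondary objective. Sample size, randomisation and the primary outcomes (fasting plasma glucose, insulin resistance, birth weight) are unaffected. It is worth correcting because it is cheap to do so before the cost data are analysed.

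**What to change.** State the cost set for each analysis before the cost data are examined:

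1. **Health insurer.** Ratio, plane and acceptability curve use insured direct health care costs plus the cost of delivering the exercise sessions, computed from the attendance that the physiotherapists record. Indirect and direct non-health care costs are left out.
2. **Patient.** Keep this declared perspective. Include out-of-pocket, time and work-absence costs only as far as the patient bears them, and say how paid-work absence is treated when income continues.
3. **Societal.** If an analysis using all direct and indirect costs is wanted, give it this label and present it separately.

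In the table of cost differences, show direct health care and direct non-health care costs on separate lines.

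The cost is a few sentences and one extra table, with the bootstrap run once per perspective. Costs are already collected by category and attendance is already recorded. The one addition that may be needed is a stated rule for separating insured from self-paid health care.

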## Discussion

The incidence of GDM is about 7% in the USA, but no accurate data on the incidence in the Netherlands are available. However, since the prevalence of overweight and obesity is increasing strongly as a consequence, an increase in the incidence of GDM is expected. Preventive strategies for women at risk for GDM are therefore of great importance. In the FitFor2-study, women with a high risk of developing GDM are identified, and given an exercise intervention, with the aim to prevent the occurrence of GDM, and perhaps also diabetes in later life.

The prevention of GDM is also relevant for the children, since it also puts the infant at risk. GDM is associated with increased risk for macrosomia, jaundice and birth trauma. Later in life, children of gestational diabetic mothers have an increased risk for obesity, abnormal glucose tolerance, and diabetes [6].

If the FitFor2 intervention program proves to be effective, pregnant women will benefit from the exercise program and a reduced risk for GDM. Obstetricians and midwives should consequently refer women at risk for GDM to a special exercise program. Implementation of the physical activity program in the Netherlands is relatively easy, since exercise programs for pregnant women under supervision of an experienced trainer are already available. These programs may have to be adjusted slightly to the FitFor2-program. Furthermore, the costs of these programs should be refunded by including them in the insurance policies.

## Abbreviations

GDM: gestational diabetes mellitus; CDC: Centers for Disease Control and Prevention; ACSM: American College of Sports Medicine; ACOG: American College of Obstetricians and Gynaecologists; RCT: randomised controlled trial; BMI: body mass index; VUMC: VU University medical centre; OLVG: Onze Lieve Vrouwe Gasthuis; SLAZ: Sint Lucas Andreas Hospital; RM: Repetition Maximum; RPE: Rate of Perceived Exertion; OGTT: oral glucose tolerance test; HOMA: homeostasis model assessment; AQUA: activity questionnaire for adolescents & adults.
